## Abstract

**Background:**

Despite the enormous investment governments allocate to fight obesity, its worldwide prevalence is still on the rise. Moreover, the majority of the programs implemented are still targeting adults struggling with overweightness and focusing on transmitting knowledge about food. However, research shows that obesity prevention is more efficacious and cheaper, and beliefs about healthy eating have a stronger influence on eating behavior than declarative knowledge about food. In fact, knowledge about healthy eating only influences weight status when combined with self-regulation competences. Thus, the main goal of the current project is to develop and evaluate the efficacy of an online preventive intervention program, the HEP-S. This program is designed to promote and develop a set of transversal skills and strategies, related to self-regulation, on the healthy eating domain among school-aged children.

**Methods:**

A three-armed randomized controlled trial will be conducted in several schools in Portugal. It will include a standard control group, with no intervention; an online intervention group, with the program for 20 weeks; and an enhanced online intervention group, with the program for 20 weeks embedded with gamification strategies throughout the program. Per research group, 40 groups of about 15 children each will be recruited and measured at five different time points. The three research groups will complete the same assessment protocol at the same timings (baseline, post-intervention, and 3, 6, and 9 months’ follow-ups). The assessment protocol will include anthropometric and psychological measures. The primary outcome measures will be the development of self-regulation skills for healthy eating over time, the development of self-efficacy attitudes, knowledge about healthy eating over time, and others. The secondary outcome measures will include the effect of gamification strategies, engagement, and satisfaction with the program, among others. The program will comprise the following: (i) a weekly group synchronous videoconference session with a trained educational psychologist serving as a mediator and (ii) a weekly parental involvement activity. Narratives, or story-tools, embedded with self-regulation strategies are at the core of the intervention.

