### Proposed sample size

Considering this longitudinal design, in the calculation of the sample, we considered a 0.25 effect size, an alpha level of 0.05, a desired statistical power of 0.8, five measures, and three research groups (i.e., control, online intervention, enhanced online intervention). To run a three-level cluster-randomized trial, previous analysis suggested 40 groups per group condition with 15 participants in each, measured at five different time points (see section “Definition of the hierarchical model”).

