### Assessment

Table 3 illustrates the timeline for the different assessment measures of the children participating in this project.

**Table 3 Tab3:** Timeline for the different assessment measures of the project

Measures	Registration (−T1)	Baseline assessment (T0)	Final assessment (T1)	3-month follow-up assessment (T3)	6-month follow-up assessment (T4)	Weekly assessment
Eligibility screen	X	–	–	–	–	–
Informed consent	X	–	–	–	–	–
Anthropometric	X	–	X	X	X	–
Sociodemographic	X	–	X	X	X	–
Self-Regulation^1^	–	X	X	X	X	–
Self-efficacy^2^	–	X	X	X	X	–
Declarative knowledge^3^	–	X	X	X	X	–
Attitudes and perceptions^4^	–	X	X	X	X	–
Healthy eating and physical activity behaviors^5^	–	X	X	X	X	–
Satisfaction	–	–	Intervention groups	–	–	–
Journal	–	Control group	Control group	–	–	Intervention groups

*X* available to all groups

^1^Self-Regulation Processes towards Healthy Eating Questionnaire

^2^ Self-Efficacy to Regulate Eating Habits for Children Questionnaire & Healthy Eating and Physical Activity Self-Efficacy questionnaire for children

^3^ Knowledge of Healthy Eating Questionnaire

^4^Students’ Attitudes and Perceptions on Healthy Eating Questionnaire

^5^ Healthy Eating and Physical Activity Behavior Recall Questionnaire for Children

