### Anthropometric measures

Children participating in the intervention and control groups will have their weight, height, and waist circumference measured by the research team at the baseline, post-intervention, and at the 3- and 6-month follow-ups. This trial does not involve collecting biological specimens for storage.

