Consider the following hypothetical values for three-level cluster-randomized trial design parameters: $$ {\upsigma}_e^2=0.5 $$, $$ {\upsigma}_{r0}^2=0.3 $$, $$ {\upsigma}_{r1}^2=0.0 $$, $$ {\upsigma}_{u0}^2=0.2 $$, and $$ {\upsigma}_{u1}^2=0.1 $$. Under the fixed slopes model, the correlation between the outcomes from different student nested within the same classroom is $$ {\uprho}_2={\upsigma}_{u0}^2/\left({\upsigma}_e^2+{\upsigma}_{r0}^2+{\upsigma}_{u0}^2\right)=0.2 $$, whereas the correlation between the outcomes measured at different time points on the same students nested within classrooms is $$ {\uprho}_1={\upsigma}_{r0}^2+{\upsigma}_{u0}^2/\left({\upsigma}_e^2+{\upsigma}_{r0}^2+{\upsigma}_{u0}^2\right)=0.5 $$. Further assumptions are as follows: (a) number of classrooms per treatment condition: *N*_3_ = 40; (b) average number of students per classroom: *N*_3_ = 15; (c) number of repeated measures per student: *N*_1_ = 5; (d) alpha significance level: *α* = 0.05; and (e) statistical power: 1 − *β* = 0.80.

Given design parameters and further assumptions, the minimum detectable effect size is 0.25. In our opinion, an effect size of Δ = .25 is a good first estimate of the smallest effect size of interest in psychological research, since it is not irrelevant and requires a considerable sample size to detect a treatment effect predicted by the researcher.

Finally, we consider that a study with 80% power is a properly powered study, despite several researchers (see, e.g., [56]) consider this a value rather low, as it entails a 20% chance of not finding a theoretically important finding.

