### Safety aspects and ethical considerations

The standard procedure to conduct studies and interventions in the Portuguese school context requires an a priori evaluation and validation of the project by the Ministry of Education before researchers can invite schools to participate. Additionally, approval of the Ethics Committee of the University of Minho was obtained and can be consulted on the trial registration. Participation in the program is entirely voluntary, and parents and children are informed that their involvement in the school’s activities will not be affected by their decision on whether or not to participate. Additionally, because there are no anticipated detrimental consequences or real risks for the participants involved in this intervention, we did not include in the current trial interim assessment, stopping rules, nor criteria for discontinuing or modifying allocated interventions. In fact, parents and children are informed they can withdraw from the program at any time. We fully recognize our responsibilities for child protection, so the project must ensure that the children who participate are safe from all forms of abuse, injury, neglect, maltreatment, and exploitation. The project will ensure an environment where children feel secure, feel free to either participate or leave the study at any time, are encouraged to talk, and are listened to. Child welfare is paramount. Hence, children are safeguarded by the adoption of child protection guidelines and by a code of conduct for all involved. In order to work with children, researchers must present their criminal records during the job application. Additionally, parental consent must be obtained before carrying any procedure with children. This protocol will be held to meet high ethical standards.

Lastly, for ethical reasons, once all the assessments have been conducted, the control group will be given the opportunity to receive the intervention. This will guarantee that all children share the same benefits of the program. In this sense, all participants will have the opportunity to develop not only knowledge but also a set of transversal skills and strategies on the healthy habits’ domain. The participation in this intervention will bring no harm, and no risks were identified. Therefore, there will be no compensation for trial participation, and no post-trial care for participants is anticipated.

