This study has some strengths worth highlighting. First, it presents an online-based intervention focused on promoting SR skills and strategies to promote healthy eating behaviors among elementary school-aged children. Second, it is conceived as a preventive approach, focused on promoting health-related behaviors, not on treatment. Third, gamification strategies will be implemented to reduce high rates of attrition and low feelings of engagement with the tool. Lastly, the research design foresees an implementation period longer than most of the intervention studies in this domain, with long follow-up. This will allow searching for sustained behavioral changes as a result of the intervention.

There are potential limitations to the present study proposal. First, although we include a weekly journal for participants to complete, during the study it will be difficult to monitor the actual implementation of the strategies trained in the program. Second, full adherence to the program will be a challenge as it implies some level of parental involvement and it lasts for 20 weeks. Third, although the study design is optimized by the selection of relevant psychological variables and the introduction of gamification strategies, the small sample size of this study confers a limited scope to examine full effects. In fact, there is the possibility that smaller effects than anticipated are found. This particular aspect may pose limitations when reflecting about the implications and conclusions of the study. Nevertheless, the study attempts to minimize this aspect by having conducted a priori power analyses. If the present trial shows positive effects at the primary outcomes level, future trials should try to use larger samples, from distinct backgrounds and cultures and include longer follow-up measures (> 6 months).

Altogether, we expect that the results of this study will provide evidence on whether training and fostering SR strategies among elementary school-aged children helps in the promotion of healthy eating habits.

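### The abstract and power calculation use five measurement occasions (the abstract runs to 9 months), but the assessment schedule has four, ending at 6 months

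*Protocol article*

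**What the plan says.** **Five occasions.** The Abstract (Methods) states "Per research group, 40 groups of about 15 children each will be recruited and measured at five different time points" and lists them, for all three arms, as "baseline, post-intervention, and 3, 6, and 9 months’ follow-ups". Proposed sample size enters "five measures, and three research groups". Definition of the hierarchical model repeats the input: "c) number of repeated measures per student: *N*_1_ = 5". Neither of these two sections mentions 9 months.

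**Four occasions.** In Table 3 (Assessment) the last follow-up column is "6-month follow-up assessment (T4"), and there is no 9-month column. The repeated questionnaires are marked at T0, T1, T3 and T4. Anthropometric and sociodemographic measures are marked at −T1, T1, T3 and T4. Anthropometric measures schedules weight, height and waist "at the baseline, post-intervention, and at the 3- and 6-month follow-ups". Primary and secondary outcome measures defines the primary outcomes at T0, T1, T3 and T4. The Discussion advises future trials to "include longer follow-up measures (> 6 months").

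**Controls.** Safety aspects and ethical considerations says that "once all the assessments have been conducted, the control group will be given the opportunity to receive the intervention".

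**The concern.** The main test is the group-by-linear-trend interaction, and the power section defines its effect size at the last time point. Whether that point is 6 or 9 months is therefore part of what the trial estimates, as well as a matter of logistics.

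Staff who follow Table 3 will collect no 9-month data. At full recruitment that is one wave of 3 × 40 × 15 = 1,800 child assessments. The published detectable effect would then belong to a design that is not run.

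There is also a conditional risk. The offer of the program to controls depends on all assessments being complete, and the documents disagree on which assessment is last. If 6 months were treated as last and a 9-month visit were wanted afterwards, an untreated 9-month comparison might not be recoverable.

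**Working it through.** **1. Can five occasions be found in the schedule?**

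- Counting registration (−T1) as a fifth occasion does not work. No measure is marked at both −T1 and T0, so each repeated outcome still has four marks. The abstract's fifth occasion is in any case explicitly 9 months.
- The weekly journal does not supply it either. It is weekly in the intervention arms only, and controls complete it at T0 and T1.
- The labels jump from T1 to T3 with no T2, but T3 and T4 are defined as 3 and 6 months, so the gap does not conceal a 9-month visit.

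**2. Inputs for the power check** (Definition of the hierarchical model)

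- N2 = 15 students per classroom (printed there as a second N3) and N3 = 40 classrooms per arm.
- ρ1 = 0.5.
- Classroom slope variance 0.1. The other variances sum to σ² = 0.5 + 0.3 + 0.0 + 0.2 = 1.0, so τ = 0.1.
- Two-sided α = 0.05 and power 0.80, so z = 1.960 + 0.842 = 2.8016.
- Assumption: visits are coded T = 0, 1, …, N1 − 1, equally spaced. Var(T) is then 2.0 for five occasions and 1.25 for four.

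**3. Reproducing the stated 0.25**

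Eq. 6 as printed multiplies the terms in the denominator. That gives a variance of 2 × 0.5 × (5 × 2.0 × 0.1) / (5 × 15 × 40 × 2.0) = 1.0/6000, and 2.8016 × 4 × 0.01291 = 0.145. This is not the stated figure.

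With a plus sign before the slope-variance term:

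MDES = 2.8016 × (N1 − 1) × √{2[(1 − ρ1) + N1·Var(T)·τ]σ² / (N1·N2·N3·Var(T))}

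For N1 = 5: 2(0.5 + 1.0)/6000 = 0.000500; SE = 0.02236; MDES = 2.8016 × 4 × 0.02236 = **0.251**. This reproduces 0.25, and power at 0.25 is 79.8%.

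**4. The same formula with four occasions**

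- *Same slope variance per visit step (0.1).* 2(0.5 + 4 × 1.25 × 0.1)/(4 × 15 × 40 × 1.25) = 2(1.0)/3000 = 0.000667; SE = 0.02582; MDES = 2.8016 × 3 × 0.02582 = **0.217**. Power at 0.25 is 89.8%.
- *Same slope variance over the whole span.* The per-step variance becomes 0.1 × (4/3)² = 1.6/9 = 0.178. Then 2(0.5 + 5 × 0.178)/3000 = 0.000926; SE = 0.03043; MDES = 2.8016 × 3 × 0.03043 = **0.256**.
- *Same growth difference per occasion.* The slope difference is 0.25/4 = 0.0625, so the effect at the fourth occasion is 3 × 0.0625 = 0.1875. With SE = 0.02582, 0.0625/0.02582 − 1.960 = 0.461, and power is **67.7%**.

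The true spacing is unequal: 20 weeks of program, then 3-month steps. These figures therefore show the range and do not replace a recalculation.

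**The case against.** The best defence is that the slip is small. The 9-month visit appears only in the abstract. Table 3, the anthropometry text, the outcome definition and the Discussion all agree on 6 months, so the cause may be one abstract phrase and one carried-over value of N1. That may be so, but the five stands in both places where the sample size is justified, so correcting the abstract alone would not be enough.

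Three stronger readings are tempting, and the documents do not support them.

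- *That the trial is powered for a 9-month effect.* The power sections say five measures and the last time point, but give no month.
- *That the trial loses power.* One scaling improves the detectable effect (0.217), one barely worsens it (0.256), and only the fixed-growth reading shows a material loss. A different reading of the formula, with the slope variance acting at classroom level and time scaled from 0 to 1, also comes near the stated figure and hardly moves: 0.245 with five occasions and 0.251 with four. No loss is shown.
- *That controls will be exposed before a planned visit.* The safety section makes the offer only after all assessments, so either schedule, applied consistently, protects the comparison. The risk exists only while the last visit is undefined.

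Nor is it true that every outcome has four occasions. Satisfaction is measured once, and the journal follows its own pattern. The count holds for the repeated questionnaires and the anthropometry.

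**Conclusion.** The contradiction stands. It concerns the number of occasions for the primary questionnaires and the date of the last one, and a separate analysis plan could not remove it from this text. The stated 0.25 at 80% power is for five occasions, while the schedule has four.

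The numerical consequence is bounded but not signed: an MDES of 0.217 to 0.256, or power of about 68% if the growth difference per occasion is held. These values rest on the plus sign restored in Eq. 6, on equal visit spacing, and on the article's hypothetical variances with no allowance for dropout. The case for correction rests on the ambiguous schedule and the mismatched power input. It does not rest on a demonstrated loss of power or on exposure of controls.

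**What to change.** Choose one schedule and carry it through the Abstract, Proposed sample size, Table 3, Anthropometric measures, Primary and secondary outcome measures, Definition of the hierarchical model and Discussion.

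- *If four occasions are kept:* delete the 9-month visit from the abstract, replace five by four in both sample-size passages, and restate the detectable effect or power with the actual visit spacing. Say whether the effect is fixed at the last visit or as a growth rate. The cost is text and one recalculation.
- *If five are intended:* add the 9-month visit to Table 3, the anthropometry text and the outcome definition, and amend the Discussion. The cost is one further assessment wave.

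In either case, name the last assessment, so that the existing rule on offering the program to controls has a definite reference point. Renumbering the time labels to close the gap at T2 is a cosmetic improvement. The article says that recruitment had not begun at submission, so at that stage the change required no rework of data already collected.

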**Discussion:**

The program may play an important role in preventing risky and unhealthy eating behaviors by focusing on the development of self-regulation skills and strategies among elementary school children.

**Trial registration:**

ClinicalTrials.gov NCT04099498. Registered on 23 September 2019.

## Introduction

### Background

Obesity is a growing epidemic affecting individuals of all generations. According to the World Health Organization, obesity has more than tripled worldwide since 1980 [1]. The rate has doubled among children and tripled among adolescents globally [1–3], with a third of European youth now having overweightness or obesity [4]. Similarly, an increasing rate of childhood obesity has also been observed in the Portuguese population. A recent study from the National Food, Nutrition, and Physical Activity Survey [5] reported that 17.3% of children below the age of 10 were overweight and 7.7% were obese. Additionally, regarding adolescents (10 to 17 years old), 23.6% were overweight and 8.7% were classified as obese [5].

Child and adolescent obesity is not only associated with medical problems such as cardiovascular disease, hypertension, metabolic syndrome, and type 2 diabetes [1, 6], but also with social and psychological risks during childhood [7]. What is more, childhood obesity is a high predictor of obesity in adulthood [8, 9]. That is, youth with overweightness and obesity have an increased risk of maintaining their unhealthy weight status into adulthood [10]. The etiology of childhood overweightness and obesity is multifactorial and the result of a combination of genetic and environmental influences [11]. Still, most cases are associated with external and modifiable factors such as eating habits and physical inactivity [12–14].

The current state of affairs shows that despite the extensive amount of investment to tackle this worrying picture, through campaigns or specific programs [15], the rates of obesity do not seem to be reverting. A plethora of interventions that worked to prevent or reduce the overweightness and obesity have been implemented and evaluated (e.g., [15, 16]). Still, the results are elusive with small improvements at best. The majority of these interventions focused on transmitting nutritional knowledge about healthy food, especially emphasizing on increased consumption of fruits and vegetables, and targeting specific behaviors, such as unhealthy eating habits and lack of physical activity (e.g., [14]). However, research shows that beliefs about healthy eating have a stronger influence on eating behavior than factual knowledge about food [17] and that providing knowledge about healthy eating only has influence on weight when combined with the promotion of self-regulation competences [18]. This suggests that the traditional approach of simply conveying knowledge on healthy eating may not be the optimal one.

Moreover, interventions often lack a theoretical background underlying the activities [16]. The field of health is witnessing a shift from a disease model to a health promotion model [19, 20]. Consequently, there is a move from a “weight reduction” to a “healthy habits education” paradigm, i.e., promote self-control and prevent excessive food intake [21]. Additionally, there is increasing evidence that remedial approaches are less effective and costlier than preventive approaches [12]. Lastly, governments and relevant stakeholders are pressured by society at large that effective prevention and health promotion programs reach more individuals, particularly children.

Amidst this scenario, information and communication technologies (ICT) are emerging as innovative and potentially cost-effective ways to respond to these challenges. ICT seems to offer the possibility of lowering the costs associated with implementing intervention programs, with the added potential benefit of reaching more individuals. In fact, eHealth interventions are spreading in many domains, including healthy eating or weight management [22]. The results of online tools or web-based programs in promoting healthy lifestyles and behaviors (e.g., fruits and vegetables consumption) and in supporting obesity treatment are very encouraging, with real potential to create a sustained impact on prevention and treatment of obesity [22]. However, despite the increasing number of online interventions on this topic and its potential on behavioral change, there is still a need of further investigation. The results of the majority of these online interventions are unclear; the designs tend to be diverse and the duration of the interventions tends to be short; and, lastly, few interventions include weight loss strategies sustained on a theoretical framework [23]. Also, the actual reach of internet-delivered interventions seems to be lower, and attrition rates higher, than expected, which reinforces the need to further explore this mode of delivering the intervention. Lastly, there are few online interventions focusing on preventive obesity approach by promoting healthy eating strategies among the general population, especially in early stages of life (e.g., children), and not only for individuals at risk or struggling with obesity [24].

